### Setting and participants

Subjects are recruited from three HIV comprehensive care clinics (CCC) in Kenya. One facility is an urban university-run clinic situated in a lower socioeconomic area of Nairobi, the second is an urban clinic attached to a faith-based hospital situated in a middle income area of Nairobi, and the third is a government-run clinic situated in a vast rural district of Kenya populated by pastoralists.

Patients are eligible to participate if they are initiating HAART for the first time (within two weeks before or after enrolment screening), if they are adults (at least 18 yrs old), if they owned or had sufficient access to a mobile phone (shared access is allowed if access is daily and the phone owner agrees to participate), and if they were able to sufficiently operate a cell phone to communicate using text-messaging (help by a partner is sufficient for illiterate subjects). Patients need to provide oral and written consent to participate. For patients who are illiterate, clear oral consent is obtained. Patients are excluded if they do not meet inclusion criteria or are not planning to attend the enrolment clinic for the planned study period (at least two years). Patients are considered newly initiating HAART if they have not taken HAART in at least one year and have not taken it ever for more than 2 months. Most prevention of mother to child transmission (PMTCT) regimens in Kenya include limited antiretroviral regimens and not true HAART, so participation in PMTCT is not an exclusion criteria. Therefore, the study covers a broad range of patients attending comprehensive care clinics (CCC) for ART in Kenya.

Participants are compensated for their participation time with money for lunch on study visit days (100 Kenya shillings). Patients are not provided cell phones or network airtime credit.

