**Methods and Design:**

A multi-site randomized controlled open-label trial. A central randomization centre provided opaque envelopes to allocate treatments. Patients initiating ART at three comprehensive care clinics in Kenya will be randomized to receive either a structured weekly SMS ('short message system' or text message) slogan (the intervention) or current standard of care support mechanisms alone (the control). Our hypothesis is that using a structured mobile phone protocol to keep in touch with patients will improve adherence to ART and other patient outcomes. Participants are evaluated at baseline, and then at six and twelve months after initiating ART. The care providers keep a weekly study log of all phone based communications with study participants.

Primary outcomes are self-reported adherence to ART and suppression of HIV viral load at twelve months scheduled follow-up. Secondary outcomes are improvements in health, quality of life, social and economic factors, and retention on ART. Primary analysis is by 'intention-to-treat'. Sensitivity analysis will be used to assess per-protocol effects. Analysis of covariates will be undertaken to determine factors that contribute or deter from expected and determined outcomes.

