### Randomization

A project statistician generated 1:1 randomization numbers for study arm assignments using a random number generating program. The randomization was stratified in a 2:2:1 ratio to the three clinics (the rural clinic having the lower number of assignments). Written allocation of assignment is sealed in individual opaque envelopes marked with study identification numbers which are distributed to all three study clinics in sufficient quantity to allocate the target numbers of participants. After consenting to participate and meeting inclusion criteria, screened subjects are enrolled and immediately afterward are assigned to the randomized study arm by a clinician opening the sealed envelopes to determine allocation. Age, gender, and CD4 T cell counts will be assessed for balance of study arm allocation at each site.

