#### Primary outcomes

The first primary outcome is patient adherence to HAART at twelve months. (See Appendix) This is assessed by self-report using a standard questionnaire of the number of pills missed in the last 30 days and calculating percent adherence based on the expected number of doses taken. Percent adherence will be analyzed as a continuous variable and dichotomous variable. Subjects are considered either 'adherent' or 'non-adherent' using an optimal adherence cut off of > 95% of medications taken as directed.[1] Adherence is assessed at each follow-up visit and 'ever-non-adherent' will be our dichotomous outcome. The twelve month scheduled follow-up (defined, allowing for non-exact timing of clinic attendance, as follow-up up to 15 months if patients not present at 12 months) is the primary analysis. The six month assessment will allow for evaluating trends but is not the primary outcome.

The second primary outcome is suppression of plasma HIV RNA load at twelve months after initiating ART. If patients are adherent to HAART regimens, absorb the drugs normally, and if their virus is not resistant to the HAART drugs in the regimen, then plasma HIV load should be suppressed to below detectable levels (≤400 copies per ml) by six months and remain suppressed thereafter. Due to variability in when patients show up for scheduled appointments, we accept follow-up on or after 20 weeks as the six month outcome visit. Analysis of 'suppressed' (≤400 copies/ml) versus 'failure' to suppress (>400 copies/ml) at twelve months as a dichotomous variable is the primary analysis. However, decrease in plasma HIV load copies from baseline to twelve month follow-up will also be analyzed as the difference in a continuous variable from baseline to twelve months.

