### Data collection

Data collection tools include a baseline questionnaire, follow-up questionnaire (used at 6 and 12 month visits), the SF-12 quality of life assessment adapted for local content, GPS co-ordinates of the clinics and participants homes, and a household roster of economic indicators. Questionnaires include continuous and categorical variables and Likert scales. All questionnaires were designed in English and translated to Kiswahili then back translated to verify meaning. Questionnaires are administered by clinic staff fluent in the languages of participants. In instances where study participants speak only local languages, the clinician translates questions directly. Antiretroviral adherence is assessed at each follow-up visit by inquiring about missed doses in the previous 30 days and calculating percent adherence according to pill counts. A visual analogue scale is used to confirm calculated adherence rates. A weekly study log is kept to record the weekly SMS messages and responses including details related to phone access, medication adherence and health or illness issues as they arose. Telephone communications with subjects in the control arm are also recorded in a similar study log, even though they are not sent the weekly SMS messages. Clinic charts are reviewed for WHO stages and clinical data on health parameters and events. A study register is kept to record follow-up.

Attempts are made to obtain lab data from samples obtained at usual clinical care time points and thus are either collected at the same visit as the study questionnaires are administered or within two weeks if not the same day. The CD4 T cell counts are run on a FACScan (Becton Dickson) at a centralized site. Plasmas for HIV viral load testing (Roche Amplicor) are separated at the central laboratory for the Nairobi clinics, but separated and frozen at -20C and batched for transport from the rural district clinic. All plasmas are frozen at -80C at the central lab. Viral loads are run in batches using manufacturer controls.

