#### Statistical methods

The intervention arm (SMS) will be compared against the control (SOC) for all primary analysis. We will use chi-squared test for binary outcomes, and T-test for continuous outcomes. For subgroup analyses, we will use regression methods with appropriate interaction terms (respective subgroup × treatment group). Multivariable analyses will be based on logistic regression (See Table 2) for binary outcomes and linear regression for continuous outcomes. We will examine the residual to assess model assumptions and goodness-of-fit. For timed endpoints such as mortality we will use the Kaplan-Meier survival analysis followed by multivariable Cox proportional hazards model for adjusting for baseline variables. We will calculate Relative Risk (RR) and RR Reductions (RRR) with corresponding 95% confidence intervals to compare dichotomous variables, and difference in means will be used for additional analysis of continuous variables. P-values will be reported to four decimal places with p-values less than 0.001 reported as p < 0.001. Up-to-date versions of SAS (Cary, NC) and SPSS (Chicago, IL) will be used to conduct analyses. For all tests, we will use 2-sided p-values with alpha = < 0.05 level of significance. We will use the Bonferroni method to appropriately adjust the overall level of significance for multiple primary outcomes, and secondary outcomes.

To assess the impact of potential clustering for patients cared by the same clinic, we will use generalized estimating equations [GEE] (ref) assuming an exchangeable correlation structure. Table 3 provides a summary of methods of analysis for each variable. Professional academic statisticians ([name]) blinded to study groups will conduct all analyses.

**Table 3 T3:** Variables, Measures and Methods of Analysis

**Variable/Outcome**	**Hypothesis**	**Outcome Measure**	**Methods of Analysis**
1) **Primary**	Intervention improved outcome from baseline to 6 months		
			
a) Adherence at 12 months		Percent adherence in previous 30 days >95% [binary]	Chi-squared test
			
b) Suppression of HIV viral load at 12 months		Viral load ≤400 copies/ml [binary]	Chi-squared test

2) **Secondary** Adherence percentage at 12 months	improvement occurred	Adherence % (>95%) [binary]	Chi-squared test

HIV viral load at 12 months	improvement occurred	Viral load (copies)	T-test

Immune reconstitution (change in CD4 T cell count from baseline)	improvement occurred	Cd4 T-cells/mm^3 ^(continuous)	T-test

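### Baseline viral load, CD4 and weight may be taken after HAART has started, which understates the change outcomes and costs precision but leaves the binary primary outcomes untouched

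*Protocol article*

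**What the plan says.** Under Setting and participants, the protocol article takes patients who are "initiating HAART for the first time (within two weeks before or after enrolment screening". The window is two-sided, so a participant may enter before the first dose or up to 14 days after it.

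Under Data collection, the aim for laboratory values is stated as "Attempts are made to obtain lab data from samples obtained at usual clinical care time points", and samples are "either collected at the same visit as the study questionnaires are administered or within two weeks if not the same day". The direction of those two weeks is not given, and the sentence concerns laboratory samples only.

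Under Randomization, "screened subjects are enrolled and immediately afterward are assigned to the randomized study arm". The abstract counts follow-up from treatment start: "Participants are evaluated at baseline, and then at six and twelve months after initiating ART". Nothing ties the baseline sample to a time before the first dose.

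Three analyses use a change from baseline:
- **Viral load:** under Primary outcomes, the "decrease in plasma HIV load copies from baseline to twelve month follow-up will also be analyzed", in addition to the dichotomous primary analysis.
- **CD4:** the Table 3 row "Immune reconstitution (change in CD4 T cell count from baseline"), a secondary outcome tested by t-test.
- **Weight and BMI:** a secondary change outcome in Table 3, also tested by t-test.

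**The concern.** Viral load falls steeply in the first weeks of HAART, and CD4 and weight may also start to move. If some baselines precede the first dose and others come two to four weeks after it, the change score mixes patients whose whole response is still ahead with patients who already have part of it behind them. The protocol expects adherent patients without resistance to be at or below 400 copies/ml by six months. For a suppressed patient, the size of the change is then set almost entirely by the baseline value.

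A sample drawn after randomisation raises a second question. Messages go out every Monday, so an intervention participant sampled two weeks after enrolment could already have received about two. Subtracting that value could remove part of any early effect. The same CD4 values also serve the check of balance between arms at each site.

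These are features of data collection. If the samples are drawn late and their timing relative to the first dose is not recorded, no later analysis wording can recover it.

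**Working it through.** The protocol gives no figure for this point, so there is none to reproduce.

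**1. Window arithmetic (all from the protocol)**
- Longest time on HAART at enrolment: 14 days.
- Laboratory sample on the same day: at most day 14. Sample up to two weeks after the visit: 14 + 14 = day 28.
- Weight is outside the laboratory window. If measured at the enrolment visit, it is at most 14 days into HAART.
- A sample taken after the enrolment visit follows randomisation.

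**2. Understatement of the viral load baseline (all inputs assumed)**

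Assume that 98% of plasma virus decays at rate k = 0.3 to 0.5 per day and 2% at 0.05 per day. After d days on HAART the baseline is too low by

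U(d) = −log10[0.98·exp(−k·d) + 0.02·exp(−0.05·d)].

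This gives U(14) = 1.61 to 1.97 and U(28) = 2.29 to 2.31 log10. Take entry as uniform from day −14 to +14, with either same-day samples or a uniform delay of 0 to 14 days:

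| Sampling | Share on HAART | Mean U | SD of U |
|---|---|---|---|
| Same day | 50% | 0.43 to 0.61 | 0.54 to 0.74 |
| 0 to 14 days later | 75% | 0.90 to 1.14 | 0.76 to 0.86 |

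**3. Variance of the change**

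With true pre-HAART value P, 12-month value F and understatement U, all independent, the observed change is F − (P − U), so its variance is Var(F) + Var(P) + Var(U).

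- Var(P) = 0.8² = 0.64 (assumed SD 0.8).
- F is set at 2.6 (log10 of 400) when suppressed, otherwise mean 4.5 and SD 0.7 (assumed). With suppression share s, Var(F) = (1 − s)·0.49 + s(1 − s)·1.9². This is 0.80 at s = 0.75 and 0.53 at s = 0.85. Those shares borrow the 75% and the 10-point gain that the Sample size section gives for adherence.
- Without on-treatment baselines the variance is 0.80 + 0.64 = 1.44, or 0.53 + 0.64 = 1.17.
- Smallest ratio: 1 + 0.54²/1.44 = 1.20. Largest: 1 + 0.86²/1.17 = 1.63.

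The variance therefore rises by about 20 to 60%, and the effective sample for this analysis falls to between 1/1.63 = 61% and 1/1.20 = 83%.

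**4. Comparison of arms**

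A separate simulation used 267 per arm, a pre-HAART mean of 5.0 and SD of 0.7, 12-month suppression of 75% against 85%, an early fall scaled to 1 or 2 log10, and 0 to 100% of patients starting before screening (all assumed except 267).
- No early SMS effect: the between-arm difference is −0.186 to −0.193 log10 in every scenario. The fall in the control arm shrinks from 1.92 to between 1.57 and 1.21 with half starting early, and to between 1.22 and 0.50 with all starting early. The SD of change rises from 1.13 to at most 1.36.
- SMS deepens the early fall by 10%: the difference shrinks to between −0.15 and −0.12 (half) or −0.12 and −0.05 (all). This applies the effect to the whole early fall, including days before randomisation when the SMS cannot act, so it overstates the dilution.

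**5. What to do with on-treatment viral loads**

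Setting them to missing leaves 50% or 25% of participants, which multiplies the variance of the estimate by 2 or 4. Keeping them and regressing the change on days on HAART (linear and quadratic terms) brings the ratio back to about 1.0. A linear term alone gives at most 1.07. In this model the decay is the same for everyone. Real variation between patients would leave some excess.

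**The case against.** The strongest reply is that the trial compares SMS with standard care and does not set out to estimate response to HAART. The windows apply equally to both randomised arms, and a two-sided entry window suits busy clinics and the aim of a broad sample. Most of this stands, and it rules out several stronger readings.

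- A reader might infer that the change outcomes no longer measure response at all. The documents do not support that: patients sampled before the first dose have proper baselines, and neither group's share is given.
- A reader might infer a biased comparison of arms. Bias needs an SMS effect before the sample is drawn. That is possible for samples taken after randomisation, but it is not shown.
- A reader might take the viral load row in Table 3 as a change score. It is a 12-month value. Viral load change appears only as the additional analysis under Primary outcomes.
- A reader might say that time to adverse drug events has no common origin. Table 1 is headed as counted from HAART initiation, which indicates one, and the exact rule may sit in an analysis plan that is not shown.
- The 28-day figure depends on reading the laboratory window forward, and samples are aimed at usual-care time points. Day 14 needs no such reading.

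The definition of baseline for analysis may also be left to the analysis plan. When the sample is drawn, however, is fixed by this document, and that part of the point remains.

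**Conclusion.** The point holds as a modest one. As written, the entry window, the laboratory window and immediate randomisation together permit on-treatment, and possibly post-randomisation, baselines for viral load and CD4, and on-treatment baselines for weight. The effect is confined to one additional analysis and to the secondary CD4 and weight/BMI change outcomes. Neither binary primary outcome uses a baseline value.

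The cost is an understated absolute change and lost precision. The 20 to 60% rise in variance rests on the assumed decay rates, SDs, suppression shares and uniform entry, and on the log10 scale, whereas the protocol speaks of copies. If few patients start HAART before screening, the loss is smaller. No size is derived here for CD4 or weight.

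**What to change.** Eligibility and the timing of treatment need not change. The changes concern sampling and recording.

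1. For participants not yet on HAART, draw the baseline sample before the first dose and before the envelope is opened.
2. For participants already on HAART, use the last pre-HAART CD4 and weight from the clinic charts, which the Data collection section already has reviewed.
3. Record days on HAART at each baseline sample.
4. Keep on-treatment baseline viral loads and adjust the change analysis for days on HAART. The linear regression already named under Statistical methods can carry this. Add a sensitivity analysis limited to pre-HAART baselines. Do not set on-treatment values to missing, which would cost more precision than the problem itself.

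The cost is a few sentences under Setting and participants, Primary outcomes and Data collection, and one derived variable. Some chart values will be absent or older than a study measurement.

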### Study design

The study is a multi-site RCT. Patients will be randomized to the cell phone (SMS) intervention group versus the standard of care (SOC) control (no SMS) at a 1:1 allocation ratio (see Figure 1 Consort diagram).

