### Intervention

The intervention being evaluated is a structured cell phone initiative to improve communications between healthcare providers and patients. The intervention protocol was conceived in 2005 by several brainstorming meetings between health care provider staff at the clinics, and ultimately incorporated feedback from pilot patients from a survey and from small group sessions[3].

Every week, on Monday mornings, the site-clinician (typically a nurse or clinical officer) sends a text message (SMS) to all subjects in the intervention arm to remind them about their support and enquire into how they are doing. Typically, a slogan is used such as "Mambo?" which is Kiswahili for "How are you?", but similar slogans in other local languages can also be used at the clinicians' discretion. To simplify their work, the clinicians use the 'send to many' function on their cell phone for mass/group messaging. Intervention subjects are instructed to respond within 48 hours either that they are doing well ("Sawa") or that they have a problem ("Shida") and request assistance. Sending an SMS is inexpensive (less than $0.05); however, in some circumstances where network credit is not available or was impractical, the patients can use the free 'flashback' function to trigger a call from the clinician. The clinician then calls to follow-up and provide triage to any subjects that respond that there is a problem, or subjects who fail to respond within two days.

Clinicians are only expected to respond to text messages during regular clinic hours, but are not restricted to do so. Intervention participants are instructed that the intervention is a clinic utility and that all emergencies should be handled through their usual means such as attending the nearest hospital emergency department. All participants receive a brief training from the clinicians on use of the phone and the protocol if they were in the intervention. Use of any of the cell phone network providers is allowed. Receiving SMS text messages or voice calls in Kenya is free on all networks.

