### Control

Patients randomized to the control arm receive their usual standard of care (SOC) clinic support but are not sent the weekly SMS slogans from the clinicians. They are, however, free to call the clinic staff at any time on their own initiative. All cell phone communications between clinicians and study participants, in both study arms, are recorded in a study log.

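### Nothing stops two participants who use the same phone from being allocated to opposite arms, which would partly expose the control patient; the dilution is probably small and a one-participant-per-handset rule removes it

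*Protocol article*

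**What the plan says.** Under Setting and participants, a patient needs a phone of their own or sufficient access to one, and "shared access is allowed if access is daily and the phone owner agrees to participate". A partner may help an illiterate patient use the phone. The exclusions are short: "Patients are excluded if they do not meet inclusion criteria or are not planning to attend the enrolment clinic for the planned study period". They do not mention a second participant on the same phone.

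Allocation is individual, "at a 1:1 allocation ratio" (Study design). Under Randomization, "Written allocation of assignment is sealed in individual opaque envelopes marked with study identification numbers", and each patient is "assigned to the randomized study arm by a clinician opening the sealed envelopes to determine allocation". The only stratification factor is clinic: "The randomization was stratified in a 2:2:1 ratio to the three clinics".

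Under Intervention, "the clinicians use the 'send to many' function on their cell phone for mass/group messaging", and the clinician telephones anyone who reports a problem or has not replied after two days. Under Control, patients "are not sent the weekly SMS slogans from the clinicians".

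The article touches on related matters in four places. Table 2 lists owned versus shared phone as a subgroup and crossover into the intervention as a potential covariate. The Control section has phone contacts logged in both arms. The clustering analysis (Sensitivity Analyses; Statistical methods) uses GEE at clinic level. The Discussion expects some contamination, but through general awareness of phone communication rather than through a shared handset.

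**The concern.** The SMS and the follow-up call go to a phone, whereas randomisation is by person. Where two participants use one phone and are allocated differently, the intervention patient's messages arrive on a handset that the control patient also uses. The text is a generic greeting that does not show whom it is for. The control patient may therefore get some of the reminder and contact that the trial means to withhold from that arm.

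Any such exposure that helps the control patient reduces the difference between arms on both primary outcomes, adherence and viral suppression. The primary test is an unadjusted chi-squared test by intention to treat, so the dilution passes straight into the main result. Crossover as a covariate does not repair it: crossover arises after randomisation, so adjusting for it does not restore the randomised comparison.

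**Working it through.** **Inputs.** From Sample size: 75% adherent under control, 85% under SMS, 247 per arm, 80% power, chi-squared test, alpha 0.05/2, two-sided. From Study design: 1:1 allocation. The article does not give the share of participants who use the same phone as another participant, so a range is assumed.

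**The plan's own figure.** The unpooled formula is n = (z_α + z_β)² × [p₁(1−p₁) + p₂(1−p₂)] / (p₂−p₁)².
- Two-sided alpha 0.05: (1.960 + 0.842)² × (0.1875 + 0.1275) / 0.01 = 247.2. The pooled version gives 250, and 247 per arm has 79.5% power.
- Two-sided alpha 0.025, the level stated: 299.4 unpooled and 303 pooled, and 247 per arm has 70.6% power.

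The stated 247 therefore matches alpha 0.05, not 0.025. That is a separate matter; both levels are shown below so that this point does not depend on it.

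**From shared phones to exposed controls.** Let s be the share of participants who use the same phone as one other participant. Among N participants there are sN/2 such pairs. With independent 1:1 allocation half are split, giving sN/4 exposed controls out of N/2. The exposed share of controls is f = (sN/4)/(N/2) = s/2.

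**From exposed controls to power.** Suppose each exposed control gains the whole 10-point effect, the worst case. The control rate becomes 0.75 + 0.10f and the difference d = 0.10(1 − f). With p̄ the mean of the two rates,

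Power = Φ{ [d√n − z_α√(2p̄(1−p̄))] / √[p₁(1−p₁) + p₂(1−p₂)] }.

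For f = 5% at alpha 0.05: p₁ = 0.755, d = 0.095, p̄ = 0.8025. The numerator is 0.095 × 15.716 − 1.960 × 0.5630 = 0.3895 and the denominator is √(0.1850 + 0.1275) = 0.5590. The ratio is 0.697, so power is 75.7%.

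| Controls exposed, f | Participants sharing, s = 2f | Difference (points) | Power, alpha 0.05 | Power, alpha 0.025 |
|---|---|---|---|---|
| 0 | 0 | 10.0 | 79.5% | 70.6% |
| 1% | 2% | 9.9 | 78.8% | 69.7% |
| 5% | 10% | 9.5 | 75.7% | 66.0% |
| 10% | 20% | 9.0 | 71.5% | 61.2% |

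**What the rows mean in patients.** With 494 analysed, s = 2% is about 10 people in 5 pairs, of which 2 or 3 are split. At s = 20% it is about 99 people in about 49 pairs, of which about 25 are split.

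**Partial effect.** If an exposed control gains only a share g of the effect, f is replaced by f × g. Ten per cent exposed with half the effect gives the 5% row.

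**The case against.** The strongest reply is that the event is rare. Both users must be adults newly starting HAART within two weeks of screening, both must plan to attend the clinic for at least two years, and both must be picked up by sampling that is not continuous (Sampling and enrolment). The owner's agreement is a condition for using the phone and does not make the owner a trial patient. This stands, and it is why the lower rows of the table should not be read as expected values.

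Several stronger conclusions might be inferred, and the article does not support them:

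- *The control patient receives the intervention.* Exposure is partial. The intervention also includes an instruction to reply within 48 hours and a call meant for that subject; a control patient is given no such instruction.
- *The definition of control is broken.* The Control section concerns what clinicians send, and the message is still addressed only to the intervention patient. What occurs is incidental exposure.
- *The owned-versus-shared subgroup is spoiled on the shared side.* In an owner and sharer pair, the exposed control may equally be the owner, who is counted under owned phones.
- *The chi-squared test is invalid because pairs are correlated.* Positive within-pair correlation raises the variance of the difference for same-arm pairs and lowers it for split pairs. With about half of each, the terms roughly cancel.

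It can also be said that the plan can examine the problem afterwards, through the contact log, the phone-ownership subgroup, home GPS co-ordinates and the household roster (Data collection). These allow inspection but do not prevent exposure. Lastly, the full protocol, which is not shown, may contain a one-per-handset check. However, the article itself sets out eligibility, exclusions and the unit of allocation, and as stated they permit split pairs.

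**Conclusion.** The point holds in a limited form. As written, the design allows two participants on one phone to be in opposite arms, and any resulting bias is toward no difference. Nothing in the primary analysis corrects it.

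The size is unknown and probably small. At 1% of controls exposed the loss is under one percentage point of power at either alpha; at 10% it is 8.0 points at alpha 0.05 and 9.4 at 0.025. These losses assume independent allocation within pairs, sharing in pairs only, and full benefit to every exposed control, so for a given f they are upper bounds. No figure is offered for viral suppression, because the article gives no assumed rates for it; the direction is the same. I rate this minor to optional: worth doing because it is cheap, not because the trial's conclusion is likely to turn on it.

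**What to change.** Add to Setting and participants that only one participant per handset is randomised. Check it at screening by comparing the patient's phone number with those of participants already enrolled in either arm. This requires numbers to be recorded for controls as well; the study register is described only as recording follow-up, so the article should say where they are kept. The rule should stop at the handset. A household exclusion would bar couples with separate phones, who are outside this problem, and a number match could not detect shared households.

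If enrolment has begun, identify split same-handset pairs from the phone numbers recorded at enrolment and add a sensitivity analysis of both primary outcomes that omits both members of each such pair. This removes one patient from each arm per pair, so it does not unbalance the comparison. Report the number of pairs found.

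The cost is one sentence and one check at screening. A few patients will not be enrolled; they continue with usual clinic care and are replaced by the next eligible patient. If the full protocol already has such a rule, stating it in the article is enough.
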